## Abstract

**Background:**

Androgen deprivation therapy leads to a number of adverse effects including deterioration of the musculoskeletal system and increased risk factors for cardiovascular and metabolic complications. The purpose of this study is to determine the effects, efficacy, retention and compliance of a physical exercise intervention in a large established cohort of prostate cancer patients from the Randomised Androgen Deprivation and Radiotherapy (RADAR) study. Specifically, we aim to compare short- and long-term effects of a prostate cancer-specific supervised exercise program to a standard public health physical activity strategy utilizing printed resources on cardiovascular and metabolic risk factors. Our primary outcomes are cardiorespiratory capacity, abdominal obesity, and lipid and glycemic control, while secondary outcomes include self-reported physical activity, quality of life and psychological distress.

**Methods/Design:**

Multi-site randomized controlled trial of 370 men from the RADAR study cohort undergoing treatment or previously treated for prostate cancer involving androgen deprivation therapy in the cities of Perth and Newcastle (Australia), and Wellington (New Zealand). Participants will be randomized to (1) supervised resistance/aerobic exercise or (2) printed material comprising general physical activity recommendations. Participants will then undergo progressive training for 6 months. Measurements for primary and secondary endpoints will take place at baseline, 6 months (end of intervention), and at 6 months follow-up.

**Discussion:**

This study uses a large existent cohort of patients and will generate valuable information as to the continuing effects of exercise specifically targeting cardiovascular function and disease risk, insulin metabolism, abdominal obesity, physical function, quality of life and psychological distress. We expect dissemination of the knowledge gained from this project to reduce risk factors for the development of co-morbid diseases commonly associated with androgen deprivation therapy such as cardiovascular disease, obesity, metabolic disease and diabetes, as well as improvements in physical and functional ability, and quality of life.

**Trial Registration:**

ACTRN12609000729224

## Background

Advancing age increases the vulnerability to cancer and the risk for other comorbid conditions (e.g. cardiovascular disease, diabetes, osteoporosis, arthritis and sarcopenia) [1] that can compromise physical function and independent living, ultimately culminating in death. The high prevalence of cancer and comorbidity-related conditions, apart from exacting a high personal, family and community cost, places a heavy burden on the health care system. Lifestyle interventions that can ameliorate toxicities of treatment, and improve ability to self care are seen as highly desirable.

Androgen deprivation therapy (ADT) leads to a number of adverse effects including deterioration of the musculoskeletal system and increased risk factors for cardiovascular and metabolic complications (e.g. negative lipoprotein profile, reduced insulin sensitivity, abdominal obesity) [2-7]. Moreover, investigators from four large recent observational studies, including our own current Australian cohort, found an increased incidence of myocardial infarction and metabolic complications following ADT [8-12]. This is of considerable concern to patients and clinicians as the co-morbidities exacerbated by ADT become a greater threat to survival than the prostate cancer itself.

Regular exercise is established for primary and secondary prevention of several chronic diseases including cardiovascular disease (CVD) and diabetes, and even premature death [13,14]. The protective effect of physical activity appears to be greater in individuals at highest risk for type 2 diabetes [15]. Notably, in regards to the risk for premature death, cardiorespiratory reserve appears to be more important than other well known CVD risk factors [16]. Men with prostate cancer undergoing ADT are recognized to gain fat mass, lose lean mass, and be subject to a series of adverse effects from therapy [5,7,9,17]. Hence these men could benefit from exercise by reducing risk factors for metabolic complications and therapy-related co-morbidities [9].

We have previously summarized all exercise interventions undertaken during and after cancer treatment [18]. Most of the experimental studies comprised patients with breast cancer and a mixture of other types of cancer, but did not include men with prostate cancer undertaking ADT [18]. Moreover, most exercise interventions included very low subject numbers, limited study designs and short-term intervention periods with modest or no follow-up periods. Recently, we [19,20] and others [21,22] in tightly controlled laboratory-based trials have demonstrated that exercise can prevent and even reverse adverse effects of androgen suppression. We have also recently reported specific exercise guidelines for prostate cancer patients that could potentially be incorporated in extensive population cohorts and community programs benefiting large numbers of patients [23]. However, to date there has been no large representative cohort study with prostate cancer patients undertaking exercise and this should be viewed as an immediate priority given the potential to reduce treatment toxicity, incidence of co-morbidity, mortality and substantially improve quality of life and well being. This study is unique as it applies findings from recent clinical trials [19-22] to a very large representative cohort of patients, the Randomised Androgen Deprivation and Radiotherapy (RADAR) study cohort. The RADAR study, examines the effect of adjuvant ADT on relapse free survival as well as other outcome measures in over 1000 men with prostate cancer at several centers in Australia and New Zealand. It will also allow us the opportunity to explore biological questions that would normally be too expensive to investigate (using data already collected by the RADAR study). The beneficial outcomes of the exercise intervention interaction, if substantiated, have the potential to alter clinical practice worldwide.

The purpose of this study is to determine the effects, efficacy, retention and compliance of a physical exercise intervention in a large established cohort of prostate cancer patients from the RADAR study. Specifically, we aim to compare short- and long-term effects of a prostate cancer-specific supervised exercise program to educational material of physical activity utilizing printed resources on cardiovascular and metabolic risk factors. Our primary outcomes are cardiorespiratory capacity, abdominal obesity, and lipid and glycemic control, while secondary outcomes include self-reported physical activity, quality of life and psychological distress. Our hypothesis is that compared to a standard physical activity recommendation (e.g. perform 30 minutes of moderate/vigorous physical activity 5 days of the week), the prostate cancer-specific supervised exercise intervention will elicit superior adaptations in: improving physical/cardiorespiratory capacity; body composition (reducing abdominal fat mass); glycemic control and lipid metabolism; enhancing self-reported physical activity, quality of life and psychological distress. This project has the potential to elicit positive health benefits for large numbers of men with prostate cancer. It is a lifestyle intervention that allows patients some control and personal responsibility and, as such, could easily be expanded to all such patients resulting in a considerable reduction in morbidity and mortality.

## Methods/Design

This is a randomized controlled trial in which all subjects will receive printed material which describes the importance of exercise for prostate cancer patients and outlines basic recommendations to increase their levels of physical activity (e.g. perform 30 minutes of moderate/vigorous physical activity 5 days of the week). However, only half of the subjects will be given access to regular sessions with an exercise physiologist and access to dedicated Internet resources over a period of 6 months (group 1). In the second 6-month period, group 1 will further have access to a booklet with detailed information about a home exercise program but will not receive exercise supervision (Figure 1). The group only receiving printed material about basic recommendations to increase levels of physical activity (control condition, group 2) will remain unchanged during the 6-month follow-up. This design is based on our experience over numerous exercise trials and has several advantages over a "no intervention" control group. First, in exercise research, subjects allocated to a true control group will either comply, drop out early, or take up exercise regardless of the instructions to maintain their usual lifestyle. The result is very low retention or worse, a severely contaminated dataset. At the completion of the study, group 2 participants (control condition) will be given access to all printed and Internet-based resources (including the booklet with detailed information about a home exercise prescription) developed during the course of the study to encourage exercise adoption.

**Figure 1 F1:**
[figure not shown]
**CONSORT diagram**.

### Subjects

370 men from the RADAR study cohort undergoing treatment or previously treated for prostate cancer involving ADT with no regular exercise (undertaking structured aerobic or resistance training less than two times per week) within the past 6 months will be recruited (Figure 1). Participants will have been treated or are currently being treated with ADT, able to walk 400-m and will require medical clearance from their physician (general practitioner). Exclusion criteria will include bone metastases, acute illness or any musculoskeletal, cardiovascular or neurological disorder that could inhibit or put them at risk from exercising. Participants with established but controlled CVD or type II diabetes will not be excluded from participation given the large benefits of exercise. Subjects will be recruited from the RADAR study database via a letter of invitation from their specialist and will then be contacted by an exercise physiologist accredited by the Australian Association for Exercise and Sport Science (AAESS) or Sport & Exercise Science New Zealand (SESNZ) in their respective geographical areas. Those entering the study will complete a health history questionnaire and undertake baseline measures prior to being randomized to either the supervised exercise group or the standard physical activity recommendation group. The protocol has been approved (ID: 3636-[name]) by the University Human Research Ethics Committee and all subjects will provide written informed consent.

### Randomization and Stratification

Patients will be randomly allocated to the two treatment arms: (1) exercise and (2) standard physical activity recommendation in a ratio of 1:1, subject to maintaining approximate balance regarding stratification for age (<69, 69-74, >74), original RADAR study arm [(A) 6-month ADT and radiation; (B) 6-month ADT, radiation and 18-month bisphosphonate; (C) 18-month ADT and radiation; and (D) 18-month ADT, radiation and 18-month bisphosphonate], current levels of testosterone (<3, 3-8, >8), and waist circumference (< or > than 102 cm) (Figure 2).

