### Exercise Intervention (group 1)

The exercise program will be undertaken twice weekly in small groups of participants and will be supervised by the exercise physiologist over 6 months. This group will also have access to Internet resources where they will be able to input information regarding their weekly physical activity. Sessions will comprise aerobic and resistance exercise using a variety of equipment. In addition, 2 exercise sessions will be completed at home each week comprising aerobic exercise (e.g. walking). The clinic sessions, which will commence with a warm-up and finish with a cool-down (comprising exercise on a cycle ergometer or treadmill at a relatively low intensity and stretching activities), will take approximately 60 minutes and will be conducted in local exercise facilities. The moderate- to high-intensity progressive resistance training regime will include 7 exercises that target the major upper and lower body muscle groups, which we have used previously in a number of studies including those with prostate cancer patients [19,24-27]. The exercises are the chest press, seated row, shoulder press, leg press, leg extension, leg curl and abdominal crunches. The resistance exercise program is designed to progress from 12 to 6-repetition maximum (RM) for 2 to 4 sets per exercise. Each clinic session will include 20-30 minutes of aerobic exercise using various modes such as walking or jogging on a treadmill, cycling or rowing stationary ergometers. Target intensity will be 70-85% of estimated maximum heart rate with individual heart rate monitors provided for each participant. During the 6-month follow-up period, this group will have access to a booklet with detailed information about a home exercise prescription but will no longer receive exercise supervision. The home exercise program combines resistance training (using body weight, rubber bands, and objects around the house as a resistance and is designed to replicate the exercises performed in the supervised sessions), aerobic training, and flexibility exercises.

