### Blood Markers

Testosterone, prostate specific antigen (PSA), insulin, lipid profile, glucose and HbA_1c _levels will be measured commercially by accredited Australian National Association of Testing Authorities (NATA) and International Accreditation New Zealand (IANZ) laboratories.

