### Additional Measures for the Perth Site

In addition to the above measures, participants at the Perth site will have the following assessments undertaken at the same 3 time points.

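### Allocation is balanced on four patient factors but not on site, so the split between arms within Perth, Newcastle and Wellington is left to chance

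*Protocol article*

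**What the plan says.** The section Randomization and Stratification gives a complete list of balancing factors with their levels. Allocation is 1:1, "subject to maintaining approximate balance regarding stratification for age (<69, 69-74, >74), original RADAR study arm" (four arms), and then "current levels of testosterone (<3, 3-8, >8), and waist circumference (< or > than 102 cm". That makes four factors with 3, 4, 3 and 2 levels. No other section says that allocation is done within or balanced by site.

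Other sections show where site enters:

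- The abstract places the trial "in the cities of Perth and Newcastle (Australia), and Wellington (New Zealand").
- Under Subjects, men are contacted by exercise physiologists accredited by an Australian or a New Zealand body, "in their respective geographical areas".
- Under Exercise Intervention (group 1), the supervised small-group sessions "will be conducted in local exercise facilities".
- Under Blood Markers, the assays, which include the lipid and glycemic primary outcomes, "will be measured commercially by accredited Australian National Association of Testing Authorities (NATA) and International Accreditation New Zealand (IANZ) laboratories".
- Under Additional Measures for the Perth Site, "participants at the Perth site will have the following assessments undertaken at the same 3 time points". These are body composition by DXA, 1-RM muscle strength, and balance.

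The analysis paragraph names t tests, correlation and regression, and a group by time repeated measures ANOVA.

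**The concern.** In a multi-site trial of a supervised intervention, site usually belongs among the allocation factors, because staff, premises and measurement tend to differ by site. Here the article fixes the list of factors explicitly and site is not on it. The point is therefore about a stated rule, not about detail that an article leaves to the full protocol.

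Three things are at stake. First, one site can by chance contribute noticeably more men to one arm than to the other. Any difference between sites in outcome level then adds to the variation of the arm comparison. Second, the Perth-only endpoints are a single-site comparison, and nothing in the allocation secures a 1:1 split, or balance on the four factors, among the Perth men. Third, the split is settled once the men are randomized. A model term can adjust for site afterwards but cannot even out the numbers.

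**Working it through.** **Inputs from the article.** 370 men, 185 per arm; 142 evaluable per arm for a 0.33 SD difference, 80% power, two-sided 0.05; three sites; factor levels 3, 4, 3 and 2.

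**Assumptions.** The article gives neither site sizes nor site differences. Site shares are taken as equal thirds, 50/30/20% or 60/25/15%. Shifts in mean outcome across the three sites are taken as 0, ±0.25 or ±0.5 SD (one site below, one at, and one above the reference). Allocation is taken as independent of site with fixed 185/185 totals.

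**1. The plan's own figure.** n per arm = 2 × ((1.960 + 0.842)/0.33)² ≈ 144.1, so 145. The plan says 142, within 3%. Power at 142 per arm is 0.79, which is the ceiling for the power figures below.

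**2. Split within one site.** With m men at a site, the number in the exercise arm is hypergeometric, with SD = √(m × ¼ × (370 − m)/369). For m = 123: √(123 × 0.25 × 247/369) = 4.54. The 95% range is 61.5 ± 1.96 × 4.54 = 61.5 ± 8.9, or about 53 versus 70. Exact hypergeometric results for other sizes:

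| Men at site | 95% range in exercise arm | P(worse than 55:45) | P(worse than 60:40) |
|---|---|---|---|
| 222 (60%) | 102–120 | 1.5% | 0.0% |
| 185 (50%) | 83–102 | 6% | 0.0% |
| 123 (one third) | 53–70 | 19% | 0.8% |
| 74 (20%) | 29–45 | 36% | 5% |
| 55 (15%) | 21–34 | 38% | 8% |

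**3. Site contribution to the arm difference in end values.** Take 142 per arm, sites of 142, 86 and 56 men, and shifts of −0.5, 0 and +0.5 SD. The between-site variance is 0.25 × (142 + 56)/284 − (0.5 × (56 − 142)/284)² = 0.1743 − 0.0229 = 0.151. The SD of the contribution is √(0.151 × (284/283) × 2/142) ≈ 0.046. Simulation (5,000 runs per scenario) gave a mean of 0, an SD of 0.046 and 95% of runs within 0.092 SD. For ±0.25 SD shifts it gave an SD of 0.023 and 95% within 0.046. The target is 0.33 SD.

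**4. Type I error and power, from the same simulation.** Without site balancing, type I error of the unadjusted test was 0.044, 0.051 and 0.056 for shifts of 0, ±0.25 and ±0.5 SD. Power at 0.33 SD:

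| Allocation and model | ±0.25 SD | ±0.5 SD |
|---|---|---|
| No site balance, no site term | 0.776 | 0.728 |
| Site balance, no site term | 0.774 | 0.747 |
| No site balance, site term | 0.789 | 0.782 |
| Site balance and site term | 0.784 | 0.792 |

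The Monte Carlo standard error is about √(0.78 × 0.22/5000) = 0.006, so gaps of about 0.01 are within noise. Balancing by site without a site term makes the unadjusted test conservative: type I error was 0.036 at ±0.5 SD. The two steps therefore belong together.

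**5. Perth-only efficiency.** Relative to an even split, 53 versus 70 keeps 4 × 53 × 70/123² = 14,840/15,129 = 0.98, a loss of about 2%.

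**6. Number of cells.** The present factors give 3 × 4 × 3 × 2 = 72 combinations (370/72 = 5.1 men each). Crossing with three sites gives 216 (1.7 men each).

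**The case against.** The strongest reply is that nothing here is invalid. Randomization without a site factor is legitimate, the site contribution averages zero, and the test already allows for chance imbalance. That stands. A reader might infer from the missing factor that the treatment effect will be biased or the false-positive rate raised; steps 3 and 4 show neither.

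Second, the stated analysis includes a group by time ANOVA on outcomes measured at baseline and twice afterwards. A constant laboratory or operator offset cancels in change from baseline, so step 3 applies only to comparisons of end values. That also stands, with two limits. The article lists t tests as well, so end-value comparisons are not excluded. Site differences in how men respond to training would not cancel.

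Third, a site term alone recovers nearly all the lost power (0.78 against 0.79), and a statistical analysis plan that is not shown may contain one. This too is right, and the absence of a site term from the article is not held against it. But a site term cannot secure even arms within Perth or an even exercise caseload at each site.

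Fourth, two national accreditation schemes do not prove that measurement or delivery differs; Perth and Newcastle both fall under the Australian one. That is fair. The size of any site difference is an assumption. The 0.33 SD target itself belongs to the 400-m walk, which laboratory differences cannot affect.

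**Conclusion.** The point holds as an avoidable weakness in a stated allocation rule, of modest size. Site is left out of a closed list of balancing factors in a trial whose supervision and facilities are local, whose laboratories fall under two national schemes, and some of whose endpoints exist at only one site. With a third of the men at Perth and fixed arm totals, a Perth split as uneven as about 53 versus 70 lies within the 95% range; smaller sites can be proportionally more uneven. For end values, the site contribution would lie within about 0.05 to 0.09 SD in 95% of allocations under assumed shifts of ±0.25 to ±0.5 SD, and largely vanishes in change from baseline if offsets are constant.

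A reader might also infer that site differences contaminate the Perth-only endpoints. They cannot, because all those men are at one site. The issue there is only that the 1:1 split and factor balance within Perth are not secured, and the uneven split itself costs about 2% in efficiency at 53 versus 70.

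Confidence is high for the omission itself. The magnitudes depend on site sizes and site shifts that the article does not give, and on allocation being unrelated to site. If the four existing factors are associated with site, some balance by site would follow indirectly.

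**What to change.** Add site (Perth, Newcastle, Wellington) to the balancing factors in Randomization and Stratification, using minimisation rather than fully crossed strata, since 216 cells for 370 men would be too sparse. The article's aim of approximate balance already accommodates this. Include site as a fixed effect in the between-group analyses, if the analysis plan does not already do so.

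The cost is one more factor in the allocation program and one more term in the model, with slightly looser balance on age, RADAR arm, testosterone and waist. It needs no extra men, visits or staff. The change to allocation is only useful for men not yet randomized; the site term can be added at any time before the analysis is fixed.

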### Calculation of Sample Size and Statistical Analysis

The sample size estimate was based on projected changes in aerobic walking capacity (cardiorespiratory fitness) as measured by the 400-m walk as this study endpoint has been shown to be a strong predictor of mortality, CVD and mobility limitations in older adults [28,40,41]. To achieve 80% power at α = 0.05 (two-tailed), 142 subjects per group are required to demonstrate a 0.33 SD difference between groups at the end of the 6-month intervention and follow-up periods. Previous experience with exercise trials indicates an attrition rate of up to 30% over the course of the study period. Therefore, to ensure that we have sufficient subject numbers at the end of the intervention and follow-up periods, 185 subjects will be randomized to each of the groups (N = 370). Regarding the other outcomes, a sample size of 370 will account for expected differences. Data will be analysed using the SPSS statistical software package. Analyses will include standard descriptive statistics, Student's t tests, correlation and regression, and two-way (group × time) repeated measures ANOVA to examine differences between groups over time. All tests will be two-tailed and an alpha level of 0.05 will be applied as the criterion for statistical significance.

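### The named between-group analyses leave out the balancing factors and use baseline at most as a level of time, so standard errors are too large and power is lost

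*Protocol article*

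**What the plan says.** Under Randomization and Stratification, the protocol article allocates 1:1 "subject to maintaining approximate balance regarding stratification for age (<69, 69-74, >74", then original RADAR arm (four levels), and "current levels of testosterone (<3, 3-8, >8), and waist circumference (< or > than 102 cm". The last paragraph of the Background lists abdominal obesity among the primary outcomes. The section on anthropometric measures assesses central adiposity by waist circumference. One balancing factor is therefore the dichotomised baseline of a primary outcome measure.

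Study Endpoints sets three measurement times: baseline, 6 months, and a follow-up 6 months later. Under Calculation of Sample Size and Statistical Analysis, "Analyses will include standard descriptive statistics, Student's t tests, correlation and regression" is followed by a two-way repeated measures ANOVA in group and time, the only method on the list tied to differences between groups over time. No covariate is named. The sample size rests on the 400-m walk and on a standardised effect of 0.33 at both later measurement times: "To achieve 80% power at α = 0.05 (two-tailed), 142 subjects per group are required".

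**The concern.** Balancing allocation on a prognostic factor removes that factor's contribution to the chance difference between arms. An analysis without the factor still counts that variance in its standard error, so intervals are wider than they need be and the true type I error falls below the nominal 5%. A t test holds no covariates, and an ANOVA in group and time has no place for the four balancing factors.

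A second loss is separate from the balancing. Using baseline as a level of time gives a change-type contrast, which weights baseline by 1 whatever its correlation with follow-up. ANCOVA estimates the weight and is never worse in large samples. The trial collects all these variables before randomization, so the lost precision is available at no cost.

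**Working it through.** **Inputs from the article.** Two-sided α 0.05; 80% power; 0.33 SD; 142 per group needed; 185 per group randomized; attrition up to 30%; waist cut at 102 cm.

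**Assumptions (not in the article).** Baseline to follow-up correlation r, shown over a range; equal SD at both times, set to 1; for waist, 102 cm falls at the median, balance is exact, all 370 men are analysed and the difference is 0.2 SD; for the walk, 185 × 0.70 = 129.5, taken as 129 completers per group.

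**1. The plan's own figure.** n = 2(1.960 + 0.842)²/δ². With δ = 0.33: 2 × 7.849/0.1089 = 144.1, so 145. With δ = 1/3: 2 × 7.849 × 9 = 141.3, so 142. The stated 142 reproduces as an unadjusted two-sample figure. It takes no credit for baseline or for the balancing factors.

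**2. Variance of each analysis, per man, in SD² units.**
- Follow-up values only: 1
- Baseline-to-6-month change (the group × time contrast): 2(1 − r)
- ANCOVA on baseline: 1 − r²

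The ratio of change to ANCOVA is 2/(1 + r): 1.54, 1.33, 1.18 and 1.11 at r = 0.3, 0.5, 0.7 and 0.8.

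**3. 400-m walk, 129 per group, 0.33 SD.** Power = Φ(0.33/√(2V/129) − 1.96), with V from step 2. At r = 0.5 the contrast has V = 1, SE = 0.1245 and Φ(0.69) = 75%. ANCOVA has V = 0.75, SE = 0.1078 and Φ(1.10) = 86%.

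| r | follow-up t test | group × time contrast | ANCOVA |
|---|---|---|---|
| 0.3 | 75% | 61% | 79% |
| 0.5 | 75% | 75% | 86% |
| 0.7 | 75% | 93% | 96% |

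At r = 0.3 the contrast does worse than a t test that ignores baseline.

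**4. Waist: type I error of the nominal 5% test.** A median split captures 2/π = 0.637 of a normal variable's variance. With balance on that split, the true variance of the difference is a fraction of what the model assumes:
- Follow-up t test: 1 − 0.637r². At r = 0.5 this is 0.841, and 1.96/√0.841 = 2.14 gives 3.3%. At r = 0.8 it is 0.593, and 1.96/√0.593 = 2.55 gives 1.1%.
- Change contrast: 1 − 0.637(1 − r)/2. At r = 0.5 this is 0.841, giving 3.3%. At r = 0.8 it is 0.936, giving 4.3%.

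A simulation of 10,000 trials per setting gave 3.4% and 1.1% for the t test, 3.4% and 4.4% for the contrast, and 4.8% and 5.0% for ANCOVA.

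**5. Waist: power at 0.2 SD, 185 per group.** With nominal SE s = √(2V/185) and the fraction f from step 4, power = Φ((0.2 − 1.96s)/(s√f)); for ANCOVA f = 1.
- r = 0.5: contrast s = 0.104, f = 0.841, power 48%. ANCOVA s = 0.090, power 60%.
- r = 0.8: contrast s = 0.0658, f = 0.936, power 87%. ANCOVA s = 0.0624, power 89%.
- Follow-up t test: 48% at both.

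**6. Adding the other factors.** In a simulation of 4,000 trials per setting, 142 per group, allocation was balanced on dichotomised baseline and on age thirds, and age was assumed to explain 10% of outcome variance. Over r from 0.3 to 0.8, type I error was 1.9% to 2.8% for the change contrast, 4.1% down to 2.9% for ANCOVA on baseline alone, and 4.8% to 5.2% with baseline plus the balancing factors.

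**The case against.** The strongest reply is that the plan does use baseline. It is one of the three measurement times, so the group × time term is a change-type comparison. This stands, and it rules out reading the plan as ignoring baseline. A reader might also take the most striking waist figures (type I error near 1%, power of 48% against 89% at r = 0.8) as properties of the planned analysis. They belong only to a t test on follow-up values, and the article does not say what its t tests compare. For the contrast at the same r, the figures are 4.3%, and 87% against 89%.

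The second reply is that the list of methods is open and includes regression, and that a journal article may leave covariates to an analysis plan. This stands in part: adjustment is unspecified, not excluded. But the article does name its tests, the one tied to group differences over time is the group × time ANOVA, and these do not match the allocation described one section earlier. Listing regression beside correlation commits to nothing.

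The third reply is that any error is conservative. That is correct: unadjusted analysis neither biases the randomized comparison nor inflates false positives. The cost is power and interval width.

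**Conclusion.** The point holds in a limited form. The named between-group methods contain none of the four balancing factors and use baseline at most as a time level. Standard errors are too large where those factors predict the outcome, and power is lost.

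The loss is material at low to moderate correlation: 18 percentage points at r = 0.3 and 11 at r = 0.5 for the 400-m walk, and 12 at r = 0.5 for waist. It is small at r of 0.8 or more. With 30% attrition, baseline adjustment about restores 80% power for the walk at r = 0.3 (79%) and exceeds it from r = 0.5 (86%).

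These sizes rest on assumed correlations, a median split at 102 cm and exact balance. The article promises approximate balance over 3 × 4 × 3 × 2 = 72 combinations, so the true conservatism may be smaller. The figures are for the baseline-to-6-month contrast, not the overall group × time test over three times. The change is worth making because it costs nothing; the trial's validity is not in question.

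**What to change.** In Calculation of Sample Size and Statistical Analysis, state that between-group differences in continuous outcomes at 6 months and at the follow-up 6 months later are estimated from an ANCOVA, or a mixed model for repeated measures, with the outcome's baseline value and the balancing factors (age group, RADAR arm, testosterone category, waist category) as covariates. Where waist is the outcome, use continuous baseline waist in place of the category. Report the adjusted difference with its 95% confidence interval, and say that Student's t tests are descriptive only.

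The factors should enter as main effects, which takes 2 + 3 + 2 + 1 = 8 degrees of freedom, plus one for the baseline value. That is negligible with about 258 completers (2 × 129). The cost is one sentence: every variable is already collected before randomization, and neither the design nor the sample size changes.
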